### Adverse event

Adverse events (AEs) will be appropriately assessed, managed, and recorded by the acupuncturists and related clinical specialists. We have set a specific questionnaire for recording AEs in real time by the REDCap EDC system. All AEs will be dealt with symptomatically. If the acupuncturist is unable to handle it, it is necessary to consult specialists of the corresponding discipline for consultation and treatment. Common acupuncture-related AEs include subcutaneous hematoma, continuous post-needling pain, and dizziness.

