Acupuncture is considered as a beneficial alternative treatment for functional gastrointestinal disorders [6]. Although whether acupuncture is an alternative treatment for IBS still remains controversial [7–11], previous studies have shown that acupuncture may affect IBS from the perspectives of the brain-gut axis, gastrointestinal motility, and visceral hypersensitivity [12, 13]. Furthermore, the recent clinical randomized trial supported that acupuncture may be more effective than pinaverium bromide for the treatment of IBS-D, with effects lasting up to 12 weeks [14]. Regrettably, the efficacy endpoints of most clinical trials of acupuncture for IBS often do not meet the current recommendations from the US Food and Drug Administration (FDA) or the European Medicines Agency. We have conducted a pilot clinical randomized trial with a minimum sample size (*n* = 90) in 2020 using efficacy endpoints that meet the current recommendations from the FDA [15]. For the primary endpoint, the composite response rates at week 4 between true acupuncture (specific acupoints and non-specific acupoints) and sham acupuncture (non-acupoints) were 46.67% and 26.67%, respectively, and the line charts trends of all endpoints of specific acupoints acupuncture are consistent and better than sham acupuncture. However, the effective response rates of different acupuncture groups and sham acupuncture group have no statistical significance, and we considered that the insufficient sample size cannot be ignored. Therefore, a large-sample, multicenter randomized controlled trial with high methodologic quality was considered necessary.

Accordingly, we designed the large-scale trial in order to provide substantive evidence on acupuncture as a reliable option. The primary objective is to evaluate the efficacy of acupuncture for the treatment of IBS, and the second objective is to assess the safety of the present acupuncture protocol.

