### Interventions

The true acupuncture (TA) group and sham acupuncture (SA) group will be set in this trial. The acupuncturists will be required to have a minimum licensed time of 3 years. Participants will receive 15 sessions of treatment overall 6-week treatment duration. Treatment will be given 3 times a week for the first 3 weeks (once every other day) and 2 times a week for the last 3 weeks (once every three days). Single-use sterile needles (0.30 mm in diameter and 40 mm in length or 0.30 mm in diameter and 25 mm in length; Hwato, Suzhou, China) will be used in the TA group. Blunt-tipped placebo needles will be used (similar to the Streitberger design) in the SA group which can provide participant-blinding effects with a similar appearance to conventional needles but no skin penetration [17, 18]. Adhesive pads will be placed on puncture points in both groups. The use of blunt-tipped placebo needles and adhesive pads is to help maximize the blinding of participants in the SA group, and adhesive pads also have the function of fixing blunt-tipped placebo needles. The research manual will be developed prior to the trial, and uniform training will be provided to all study staff (including acupuncturists), in areas such as recruitment, evaluation of outcomes, positioning of acupuncture acupoints, and acupuncture manipulation. During the treatment phase, each sub-center will have 1–2 acupuncturists implementing both groups of the intervention. We will require the acupuncturist to be responsible for the complete treatment of each patient rather than requiring the acupuncturist to specialize in a particular group of treatments, so that patients will not be able to differentiate between the treatment groups through the acupuncturist. In addition, patients assigned to the placebo group will be offered a free acupuncture treatment at the end of the follow-up period if they wish.

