### Randomization, sequence generation, and blinding

Eligible participants will be randomly assigned to the TA group and SA group according to the ratio of 1:1 by central stratified block randomization in the REDCap EDC system with a dynamic block size. The randomization sequence was created by a biostatistician who did not participate in this trial. Recruiters will be responsible for registering the participants, and acupuncturists will assign the participants to the intervention. The different REDCap EDC system permissions depend on the role of the personnel. Only the acupuncturist and his or her assistant can obtain the randomization grouping information. The clinical recruiters, outcome assessors, data managers, and statisticians will be blinded to the group allocation.

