### Statistical analyses

The following hypothesis will be tested simultaneously for the primary outcome:H0: There is no difference in the response rate between the TA and SA groups.H1: There is a significant difference in the response rate between the TA and SA groups.

All analyses related to the treatment efficacy will be based on the intention-to-treat (ITT) population, defined as all randomly assigned participants with baseline data. Safety analyses will be based on the safety population who have received at least one treatment after randomization and have safety indicator records. Missing data will be imputed using multiple imputation.

Continuous data will be represented by mean ± standard deviation (M±SD) or median combined with interquartile range, while categorical data will be represented by frequency, constituent ratio, and percentage. For the primary endpoint, the chi-square test will be used for the comparison of the two groups. For the secondary endpoints, Student’s *t* test or Wilcoxon rank-sum test will be used to assess the continuous variables between group comparisons, and the chi-square test or Fisher exact tests will be used to evaluate the categorical variables between the groups. The safety population will be used to analyze the incidence of AEs between the groups. The *P* value less than 0.05 will be considered as statistically significant. All analyses will be performed using SAS 9.3.

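### Adverse events are recorded first-line by acupuncturists who know the allocation, so the between-arm comparison is open to differential ascertainment of unknown direction and size

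*Protocol article*

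**What the plan says.** The section on adverse events names the recorders: "Adverse events (AEs) will be appropriately assessed, managed, and recorded by the acupuncturists and related clinical specialists". It then describes when the specialists come in: "If the acupuncturist is unable to handle it, it is necessary to consult specialists of the corresponding discipline for consultation and treatment". It also names a tool: "We have set a specific questionnaire for recording AEs in real time by the REDCap EDC system". It does not say who completes that questionnaire.

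The section on randomization and blinding says who knows the arm: "Only the acupuncturist and his or her assistant can obtain the randomization grouping information". It also lists who does not: "The clinical recruiters, outcome assessors, data managers, and statisticians will be blinded to the group allocation". None of the roles on the blinded list is given the AE record.

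The Interventions section adds that "each sub-center will have 1–2 acupuncturists implementing both groups of the intervention", so each acupuncturist treats real and sham patients knowing which is which.

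The Background says that "the second objective is to assess the safety of the present acupuncture protocol", and the statistical section says: "The safety population will be used to analyze the incidence of AEs between the groups". The outcomes section has AEs recorded during the six treatment weeks and the twelve weeks after them.

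**The concern.** The incidence comparison is a fair estimate of the difference in harm only if an event has the same chance of being noticed, asked about and entered in each arm. Here the first person to do that knows the arm. Two of the three common acupuncture-related events that the protocol lists, pain that persists after needling and dizziness, depend on whether the patient is asked and on a judgement about whether the complaint is worth entering.

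An acupuncturist who knows that the sham needle did not pierce the skin might ask less after sham, which would exaggerate the harm of real needling. The same person might regard soreness after real needling as expected and not enter it, which would hide harm. Both are plausible and they pull in opposite directions.

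At stake is how far a reader can trust the answer to the second objective. The monitoring board also relies on AE data, since it may end the trial early on adverse events alone.

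**Working it through.** The plan has no figure to reproduce on this point. It gives no expected AE rate and no precision target for safety. Its sample size figures (222 evaluable, 280 randomised) concern the composite response and do not enter. The check is a comparison of sections of the protocol article.

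1. **Who records.** Acupuncturists together with related clinical specialists (Adverse event).
2. **In what order.** Specialists are consulted when the acupuncturist cannot manage the event (Adverse event). An event that the acupuncturist does not elicit or enter has no stated route to a specialist. The specialists are thus a referral route and not a second, independent source.
3. **Who knows the arm.** The acupuncturist and the assistant, and nobody else (Randomization, sequence generation, and blinding). On that wording the specialists have no access, although they are not on the list of blinded roles either.
4. **Who is blinded.** Recruiters, outcome assessors, data managers and statisticians (same section), and the participants through the placebo needle and adhesive pads (Interventions). No section gives any of them the AE record.
5. **What the record is used for.** A between-arm comparison of AE incidence in the safety population (Statistical analyses), serving the second objective (Background).
6. **Whether the limitation is disclosed.** The Discussion concedes that acupuncturists are unblinded, but only as something that may influence the intervention effect. It does not mention AE recording.

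From 1 to 3, first-line ascertainment rests with a role that knows the arm. From 4, no blinded source is named as a check on it. From 5, the result is compared between arms. From 6, the consequence for safety data is not acknowledged. The comparison is therefore open to differential ascertainment. Nothing in these sections shows that such bias will occur, or which way it would go.

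**The case against.** The strongest case on the other side has five parts.

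- **The acupuncturists are not the only recorders.** This stands as a correction. A reader might infer that an unblinded provider alone holds the AE record. The protocol names specialists too, and its access rule implies that they do not know the arm. It does not make them an independent source, for the reason given in step 2.
- **There are safeguards.** Participants are blinded, so what they volunteer does not depend on knowing their arm. There is a dedicated questionnaire in real time, the same acupuncturists treat both arms, and data edits are traceable. These reduce the risk. They do not remove the recorder's knowledge of the arm.
- **Operational detail may sit elsewhere.** A journal article may leave to the full protocol or the research manual who completes the questionnaire and who asks about events in follow-up, when there are no treatment sessions. That is fair, so the point rests on what the article does state: who records and who knows the arm. It bears most directly on the six treatment weeks.
- **Judgements of relatedness do not matter here.** A reader might infer that unblinded causality judgements bias the planned comparison. The stated analysis is of AE incidence, with no separate analysis of treatment-related events. Attributing an event differently does not change whether it is counted, so this argument is not used.
- **The size is unknown.** A reader might want to show a large effect by assuming capture rates. The answer then depends wholly on the assumption. With 140 per arm and equal true risk, recording 90% of events in one arm and 70% in the other raises the chance of a false p < 0.05 from 5% to about 7% at a true risk of 5%. Recording 90% against 50% at a true risk of 20% raises it to about 49%. None of these inputs is in the documents, so the figures do not support the point.

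It is also fair to say that keeping AE questions away from the efficacy assessors protects their blinding, because a hematoma or needling pain can suggest the arm. The fix has to respect that.

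**Conclusion.** The point holds in a limited form. AEs are ascertained first-line by a role that knows the allocation, with specialists as a referral route, and the resulting incidence is compared between arms in service of a stated objective. The comparison is open to differential ascertainment, and the documents do not allow its direction or size to be estimated.

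This is a weakness in a stated design choice. It is neither a contradiction nor a wrong figure. It leaves the primary endpoint, its test and the sample size untouched. A reader might go further and infer that the safety results will be biased, or that the monitoring board's decisions will be wrong. The protocol supports neither reading: it gives no evidence of unequal recording and does not say how the board will use the AE record.

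The conclusion assumes that the full protocol or manual does not already give AE elicitation to a blinded source. If it does, the article needs only a sentence saying so. The change is worth making because it is cheap and the article reports that the trial is still recruiting.

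**What to change.** Leave the real-time recording and management of AEs by acupuncturists and specialists as planned. Add to it as follows.

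- Give the existing REDCap AE questionnaire, in identical fixed wording for both arms, at the assessments already scheduled for weeks 2, 4, 6, 10, 14 and 18.
- Have the blinded participants complete it themselves, or have blinded staff ask it only after that visit's efficacy outcomes have been recorded. Self-completion is preferable, because asking after scoring protects only the current visit if an answer hints at the arm.
- Report between-arm AE incidence from this blinded-source record beside the incidence from all sources. If the two comparisons diverge, the reader can see that unblinded recording may have played a part.
- Extend the limitation in the Discussion about unblinded acupuncturists to cover AE recording.

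The cost is a few minutes per visit, using a form, a system and a schedule that already exist. Scheduled questioning loses some brief events to recall, which is why the real-time record stays. Needle-site events may still suggest the arm to whoever sees the answers, so the protection is partial.

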## Discussion

Although IBS has been extensively studied, its uncertain pathophysiology and unsatisfactory treatments prompted a growing demand for alternative treatments, including acupuncture. This large-scale trial will evaluate the efficacy and safety of acupuncture for the treatment of IBS.

For this trial, the application of blunt-tipped placebo needles, adhesive pads, and REDCap EDC system will enable the trial progress to better achieve the methodological demand for randomization, allocation concealment, and blinding of participants, clinical recruiters, outcome assessors, data managers, and statisticians. Meanwhile, we will assess the participant expectation and blinding which seems have an influence on acupuncture effects. Additionally, the primary endpoint which complies with the FDA standards will make the trial results more convincing. To the best of our knowledge, no prior RCT using FDA-recommended indicators to compare the effect between true acupuncture and sham acupuncture on IBS-D.

The intestinal microbiota is currently a popular area of research. Studies on intestinal microbiota of IBS found that patients with IBS had a higher abundance of the phylum Firmicutes and lower abundance of Bacteroides compared with healthy controls [27, 28], and the fecal microecological diversity of various subtypes of IBS patients was different [29]. In addition, Quigley et al. have suggested that the over-reproduction of intestinal microbiota may be an important factor in the induction of IBS [30]. Changes in the intestinal microbiota are closely related to IBS; however, there are no studies to confirm the regulatory effect of acupuncture on the intestinal flora of IBS. Moreover, symptoms of IBS are considered as disorders of the nervous system of the brain, and fMRI is an effective method to explore abnormal brain functions. Some researchers have used fMRI to investigate the potential mechanism of IBS, but the results are not completely consistent [12, 31]. Therefore, we will retain their stool samples and fMRI data according to the willingness of the participants to explore the possible mechanisms of acupuncture treatment of IBS.

There are several limitations in this trial. First, a previous study put forward that 6 sessions of treatment of acupuncture over 3 weeks may have been insufficient [32], so we chose the 15 sessions of treatment overall 6-week treatment period to achieve maximum effect from acupuncture. This may be more in line with actual clinical practice in China, but it may be difficult to implement in other countries due to treatment costs, commuting, and travel time. Therefore, we have made modifications for per week sessions (i.e., 3 or 2 sessions of treatment per week) to explore a standardized acupuncture protocol for IBS. Second, this trial failed to blind acupuncturists which may affect the effect of interventions between the groups. Third, although interventions in the SA group have no manual operation of skin penetration, they cannot eliminate the placebo effect completely, which should be taken into consideration when drawing conclusions.

### Trial status

This trial is currently recruiting patients.

### Registration

Chinese Clinical Trial Registry: ChiCTR2100044762. Registered on 26 March 2021.

### Protocol

There was no public or patient involvement in the design of the protocol. This is the second protocol version revised on 11 April 2022. The trial registrar will make changes to the content of the trial protocol (e.g., changes in eligibility criteria, analysis plans) in real time in the Chinese Clinical Trial Registry (http://www.chictr.org.cn/).

## Data Availability

Following the publication of this study, the authors will communicate the trial results to participants, healthcare professionals, the public, and other relevant groups. The corresponding author can be contacted to obtain data according to reasonable requirements.

## Abbreviations

REDCap: Research Electronic Data Capture
IBS-D: Diarrhea-predominant irritable bowel syndrome
IBS: Irritable bowel syndrome
FDA: Food and Drug Administration
EDC: Electronic data capture
TCM: Traditional Chinese medicine
TA: True acupuncture
SA: Sham acupuncture
IBS-SSS: IBS Symptom Severity Scale
IBS-QoL: IBS Quality of Life
PHQ-9: Patient Health Questionnaire-9
AR: Adequate Relief
fMRI: Functional magnetic resonance imaging
eCRF: Electronic case report form
DSMB: Data Safety and Monitoring Board
ITT: Intention-to-treat
M±SD: Mean ± standard deviation
AEs: Adverse events
